### Economic evaluation

Costs and benefits to the employee, employer and society will be estimated in both study groups. Costs due to lost working time will be analysed separately taking into account the compensation to the employer during full- or part-time sick leave. Data on costs of the used health services, medications, and medical aids (due to the main health problem) will also be collected. In addition, the analysis will include the compensation of the lost work input using stand-ins (salary, training time) or overtime (performed by the colleagues of the study subjects), as well as the time the supervisor used for work arrangements.

The non-monetary benefits will be studied based on self-assessed productivity at work [26], as well as the reduction of pain and disability measured on a scale from 0 to 10 (Table 2). If there is a difference between the groups in the outcome measurements, a cost effectiveness analysis will be performed dividing the costs by the units of difference in the outcome. If there is no significant difference between the study groups in any of the health related outcomes, the analysis of total costs in both groups will be applied in making the final conclusions.

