### Outcomes

The main outcomes are the number of days from the initial visit to the return to regular work activities and the total number of part- and full-time sick leave days during one- and two-year follow-up. Other outcomes are changes in symptoms as well as in self-assessed functioning during follow-up [15-17].

Data on self-assessed workload will be collected after the initial visit and during part-time sick leave in order to recognise physically strenuous work tasks relevant to MSDs [18,19], as well as to list the work adjustments made during the part-time sick leave. This will be included in an internet based questionnaire together with the symptoms and background variables [20-25]. The questionnaire will be sent to the employees immediately after recruitment and at one, three, eight, 12 and 52 weeks. Those without access to internet will be telephone-interviewed by a researcher. Also, the supervisors in both groups will be interviewed by phone after the employee has returned to work.

Participating employees, their supervisors, OH personnel, human resources management, as well as occupational safety and trade union representatives will be interviewed, and the feasibility of early part-time sick leave will be evaluated based on the qualitative information collected in the interviews. From those employees, who decline to participate, only information on age and gender will be collected. They will also be offered a possibility to provide the main reason for not participating. This can be done with an anonymous questionnaire that can be returned in a closed envelope directly to the researchers. The reason for a negative response from the supervisor is also documented.

The follow-up is extended to two years with the purpose of detecting the possible longer-lasting effects on e.g. illness behaviour. One and two years after the initial visit, the dates and diagnoses of all sickness absences (including those prescribed outside OH services) will be collected from the OH units.

Patient enrolment started in January 2008 and it is planned to last until July 2009. Follow-up of the last participants will finish two years later in 2011. Based on the pilot study, however, preliminary results on the feasibility of early part-time sick leave will be available already in 2008.

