### Statistical methods

A survival analysis will be used to study the time to return to work in the intervention and control group. The amount of sick leave days will be analysed at 12 and 24 months, and the associations between the outcomes and background variables will be analysed using general linear models. In addition, the change in symptoms and disability indices will be studied at various time points using general linear models for repeated measurements.

Subgroup analyses will be performed in relation to patient compliance, type of work, adequacy of work adjustments, previous sick leaves, pain characteristics (such as localisation, duration), and level of disability at baseline. All analyses will be made based on an intention-to-treat principle.

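### The cost-effectiveness ratio is formed only if some unnamed outcome differs between the groups, so it can be triggered by chance and its denominator is selected on significance

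*Protocol article*

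**What the plan says.** The Economic evaluation section of the protocol article sets a rule with two branches.

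- **Ratio branch:** "If there is a difference between the groups in the outcome measurements, a cost effectiveness analysis will be performed dividing the costs by the units"; the calculation is described in full as "dividing the costs by the units of difference in the outcome". The condition speaks of outcome measurements in the plural. The denominator is a single outcome that is not identified.
- **Costs-only branch:** "If there is no significant difference between the study groups in any of the health related outcomes, the analysis of total costs in both groups" is what the final conclusions rest on.

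The sentence before the rule gives the candidate benefits: "The non-monetary benefits will be studied based on self-assessed productivity at work [26], as well as the reduction of pain and disability". Table 2 lists pain intensity, interference with work, interference with sleep, self-assessed functioning and productivity. On timing, the Outcomes section says: "The questionnaire will be sent to the employees immediately after recruitment and at one, three, eight, 12 and 52 weeks", which is five waves after baseline. Under Statistical methods, "the change in symptoms and disability indices will be studied at various time points" with repeated-measures linear models. The Sample size section gives 0.05 as the significance level, and no other error level appears.

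**The concern.** A cost per unit of effect can be interpreted only if the unit was chosen before the data were seen. Here one significant result among several opens the ratio branch, and the only denominator described is an outcome that differed. Two things follow.

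1. With no true effect on anything, the trial can still produce a cost-effectiveness ratio, and it does so more often than the 0.05 level suggests.
2. When a small effect exists, the ratio is formed only in the samples where the estimate came out large enough to be significant, so the denominator is too large on average.

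This is more than detail left to a fuller document. The article states the rule, and a later plan could remove the selection only by replacing it.

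The branches also do not match. The first speaks of a difference without defining it, and the second of a significant difference in health-related outcomes. Productivity is a candidate benefit but may not count as health-related. I read both branches as turning on significance.

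**Working it through.** The plan gives no figure of its own for this point beyond the 0.05 level. One named measure tested at that level gives a 5% chance of a trigger when there is no true effect.

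**Inputs from the article**
- Candidate measures: 3 if only those named in Economic evaluation count (productivity, pain, disability), and 5 if each Table 2 measure listed above counts.
- Follow-up waves: 5 (weeks 1, 3, 8, 12 and 52).
- Level: 0.05.
- Size: 300 per group with 10 to 15% drop-out. At 10%, 300 × 0.90 = 270 per group.

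**Assumptions**
- Two-sided tests, one comparison per measure and no multiplicity adjustment.
- Equal correlation ρ of 0.5 to 0.7 between the test statistics.

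**Step 1. Chance of at least one significant result with no true effect**

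Independent tests give 1 − 0.95^k. For equally correlated tests the chance is 1 − ∫ φ(x) [Φ((c − √ρ·x)/√(1−ρ)) − Φ((−c − √ρ·x)/√(1−ρ))]^k dx, with c = 1.96.

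| Measures k | Independent | ρ = 0.5 | ρ = 0.7 |
|---|---|---|---|
| 1 | 5.0% | 5.0% | 5.0% |
| 3 | 14.3% | 12.5% | 10.9% |
| 4 | 18.5% | 15.6% | 13.0% |
| 5 | 22.6% | 18.3% | 14.8% |

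Across 3 to 5 measures and ρ of 0.5 to 0.7, the range is about 11 to 18%.

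If every wave were tested separately, 4 measures × 5 waves would be 20 tests. Simulation gives 48% (ρ = 0.5 between measures and between waves), 41% (0.5 and 0.7) and 35% (0.7 and 0.7).

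**Step 2. Size of a denominator that is used only when significant**

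Let the true effect be m standard errors and take one test. Ignoring the negligible wrong-direction tail, the mean estimate given significance is m + φ(1.96 − m)/Φ(m − 1.96).

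- m = 1 (power 17%): 1 + 0.2517/0.1685 = 2.49, or 2.5-fold.
- m = 2 (power 52%): 2 + 0.3986/0.5160 = 2.77, and 2.77/2 gives 1.4-fold.
- m = 2.8 (power 80%): 2.8 + 0.2803/0.7996 = 3.15, and 3.15/2.8 gives 1.1-fold.

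With 270 per group, 1 standard error is √(2/270) = 0.086 standard deviations. The three cases are therefore true standardised differences of about 0.09, 0.17 and 0.24.

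**Step 3. What choosing the largest difference would add**

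If the largest of 4 differences were chosen at ρ = 0.5, simulation gives about 2.6-fold at m = 1, 1.5-fold at m = 2 and 1.3-fold at m = 2.8. At low power, nearly all the exaggeration comes from requiring significance (2.49 against about 2.6) and little from choosing among outcomes.

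**Step 4. Direction of the effect on the ratio**

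If the incremental cost is positive, a denominator that is too large makes the cost per unit look too low. If it is negative, which is plausible since the Objectives section expects fewer disability days, the same error pulls the ratio towards zero and does not flatter the intervention. With no true effect, a chance trigger is as likely to point to harm as to benefit.

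**The case against.** The strongest reply is that an article condenses a fuller protocol or plan, which may name the effect measure, the time point and a multiplicity adjustment. That stands in part. The article is silent on adjustment, so its absence is my assumption. But an adjustment would only bring the false-trigger rate back to 5% or below. The ratio would still be formed only when the effect is significant, because the published rule says so.

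Three stronger readings are tempting, and the article does not support them.

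- *The largest observed difference becomes the denominator.* No passage says this. The wording fits equally well with one ratio for each outcome that differs.
- *The chance of a false trigger is around one half or more.* The 35 to 48% figures need a separate test at every wave. Repeated-measures models may give one group comparison per measure, although studying change at several time points leaves wave-specific tests open. Twenty independent tests would give 1 − 0.95^20 = 64%, but independence between repeated measurements on the same person is not credible.
- *Cost per unit will look about 2.5 times too favourable.* That factor belongs to a very small true effect tested with 17% power. It shrinks to 1.1 at 80% power, and its direction depends on the sign of the incremental cost.

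The reach is also limited. This is a secondary analysis, the main outcomes and their analyses are untouched, and the section promises cost and benefit estimates for both groups in either case.

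**Conclusion.** The concern holds in this form: the article makes the type of economic analysis depend on which unnamed outcomes differ, and it conditions the ratio's denominator on significance. Under the assumptions listed in the working, the chance trigger is about two to four times the 5% that one named measure would carry. The average exaggeration runs from 1.1-fold for a well-powered effect to 2.5-fold for an effect of 1 standard error. The number of measures, the correlations and the true effects are assumptions, because the article gives none of them. The selection on significance follows from the rule itself once a difference is read as a significant difference. Whether the ratio ends up looking too good or too poor cannot be settled from the article.

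**What to change.** In Economic evaluation, replace the two-branch rule with these points:

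- Name one effect measure and one time point in advance, for example change in pain (0 to 10) at 52 weeks. Days to return to work is a less suitable choice, because it may overlap with the lost-working-time costs already in the numerator.
- Estimate the incremental cost and the incremental effect on that measure, with their joint uncertainty, whether or not any outcome is significant. Naming the measure without this step would leave the selection on significance in place.
- Label ratios on other outcomes or time points as exploratory, and report all of them.

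This takes a few sentences, with no new data and no additional employees. The price is that the ratio may be very imprecise when the effect is near zero, and that it cannot be moved to another outcome afterwards.

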### Sample size

A 10% difference between intervention and control group in the proportions of employees returning to regular work at a given time point will be considered significant. The power of the study is aimed at 80%, and the level of significance at 0.05. Assuming a drop-out rate of 10–15%, 600 employees will be needed for the study (300 in both groups). Using previous information on sickness absenteeism in Finnish enterprises, and to ensure a sufficient pool of subjects, we will include in the study base a sufficient number of companies employing up to 30 000 persons.

### Randomisation

Employees will be randomised using sealed opaque envelopes, which contain information on the allocated group. The allocation has been performed at the Finnish Institute of Occupational Health using a random number generator and block randomisation in order to obtain equal size of intervention and control group for the participating physicians.

### Blinding

Due to practical and ethical reasons neither the employee nor the physician will be blinded to group assignment during the initial visit. Allocation is also open to the two interviewers and to the other possible physicians during later visits.

### Statistical methods

A survival analysis will be used to study the time to return to work in the intervention and control group. The amount of sick leave days will be analysed at 12 and 24 months, and the associations between the outcomes and background variables will be analysed using general linear models. In addition, the change in symptoms and disability indices will be studied at various time points using general linear models for repeated measurements.

Subgroup analyses will be performed in relation to patient compliance, type of work, adequacy of work adjustments, previous sick leaves, pain characteristics (such as localisation, duration), and level of disability at baseline. All analyses will be made based on an intention-to-treat principle.

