**General exclusion criteria**
- acute infections
- major accidental injury
- active inflammatory arthritis
- suspected occupational injury or disease
- malignant tumour diagnosed or treated during the preceding year
- severe mental disorder
- pregnancy
- severe pain (> 7 on a scale from 0 to 10)
- pain interferes with sleep severely (> 7 on scale from 0 to 10)

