### Interventions

During the initial visit, the OH physician will inform the employee about the study and its aims. If the employee agrees to participate, informed consent will be signed. It includes a permission to contact the supervisor, preferably during the same visit, in order to verify whether the work-related arrangements for part-time sick leave are feasible, in case the employee is allocated to the intervention group. If the supervisor disagrees, the employee will be excluded from the trial.

Once the agreements from the employee and the supervisor have been obtained and before the randomisation has occurred, the physician will determine the length of the sickness absence based on symptoms (Table 2), clinical findings [12,13] and background information (Table 3). If the employee is allocated to part-time sick leave (intervention group), daily work load will be reduced by restricting work time. Also, if necessary, remaining work tasks will be modified so that working should be possible despite the symptoms. In the control group, work load will be eliminated with full-time sick leave. Both groups will receive appropriate medical advice, and the need for medical treatments and a control visit will be determined as usual.

**Table 2 T2:** Health-related variables inquired at baseline and during follow-up

**Outcome**	**Measure**
Main reason for the visit (at baseline)	Localisation and characteristics of pain
Pain intensity	Scale from 0 to 10
Interference with work activities	Scale from 0 to 10
Interference with sleeping	Scale from 0 to 10
Self-assessed functioning	Oswestry Back questionnaire [15] Quick DASH (Disabilities of the Arm, Shoulder and Hand) [16] COAT (Comprehensive Osteoarthritis Test) for lower extremities [17]
Productivity at work	Quantity and Quality of work [26]
Adjustments at work (during follow-up)	Description of change in physical work load (structured and open questions)

**Table 3 T3:** Explanatory variables measured at baseline

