## Discussion

The target of this intervention is to adjust work (both work time and demands) to accommodate the disabled employee so that he or she can continue working during recovery from a MSD. As pointed out by Durand et al [27], in this type of intervention work becomes an object of the intervention itself raising various methodological challenges. In addition to the medical judgement by the physician, the intervention requires actions and decisions made by the employee, supervisor, colleagues and employer – each with their own values, objectives, interests, and training [28].

Sickness absence is usually considered as a consequence of a health disorder rather than its treatment and, therefore, in most studies, it has been used as an outcome measure. In this trial, however, the mode of sick leave (part- or full-time) is used as an intervention to affect the outcome, i.e., the quantity of sick leave (number of sick leave days). The potential benefit of the intervention, i.e., the difference in the total number of full- or part-time sick leave days between the intervention and control group, will arise either from the employee's decision to return to regular work earlier than recommended by the physician, or from the need for additional part- or full-time sick leave during the follow-up period.

It is essential in this intervention that the physician determines the length of the disability before allocation, and adheres to this when prescribing either part- or full-time sick leave. This is to avoid bias that might occur if the length of the sick leave is determined differently for part- and full-time sick leave. The risk for bias concerns also the possible control visit, during which the allocation to further part- or full-time sick leave is again open to both the physician and the employee. Inappropriately timed return to regular work in either group should, however, show in secondary outcomes, such as pain, functional status, employee satisfaction and costs.

Despite the extensive amount of quantitative data collected in this trial on individual, ergonomic, psychosocial and economic factors, we do not have the means to quantify all the aspects of the arrangements made at the workplaces during part-time sick leave. Acknowledging the potential effect of this contextual process on the outcome of the intervention, we aim to collect all relevant qualitative data during the study from the employee and the supervisor.

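### Symptom and disability outcomes are analysed as change with no baseline adjustment stated, which can lose precision but not gain it and leaves these secondary comparisons open to chance baseline imbalance

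*Protocol article*

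**What the plan says.** The protocol article's Outcomes section lists the health outcomes after the two main ones: "Other outcomes are changes in symptoms as well as in self-assessed functioning during follow-up". The Statistical methods section gives the analysis: "the change in symptoms and disability indices will be studied at various time points using general linear models for repeated measurements". The same section mentions general linear models for associations with background variables, but it does not say that the group comparison of symptoms is adjusted for the starting score.

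A starting score is available. Table 2, in the Interventions section, is titled "Health-related variables inquired at baseline and during follow-up" and covers pain intensity, interference with work and sleep, and the functioning questionnaires. The later time points are fixed too: "The questionnaire will be sent to the employees immediately after recruitment and at one, three, eight, 12 and 52 weeks".

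The Discussion gives these outcomes a specific job: "Inappropriately timed return to regular work in either group should, however, show in secondary outcomes, such as pain, functional status, employee satisfaction and costs".

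**The concern.** Subtracting the baseline fixes its coefficient at 1. In employees who consult with pain and mostly recover, the starting score is likely to predict later scores only in part. Subtraction then adds baseline noise to each follow-up comparison. It also over-corrects for imbalance, because the arm that happens to start higher appears to improve more through regression to the mean. Entering the baseline as a covariate lets the data set the coefficient.

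These outcomes are secondary, but the plan leans on them in two places. The Discussion treats pain and function as the check on a badly timed return to work, in a trial where later leave decisions are made with allocation known. The Economic evaluation section counts reduced pain and disability as a benefit, and lets the form of the economic analysis depend on whether any health outcome differs significantly between the groups. A needlessly imprecise comparison makes it more likely that a real difference, in either direction, is missed.

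**Working it through.** **Inputs.** From the Sample size section: "The power of the study is aimed at 80%, and the level of significance at 0.05" (taken here as two-sided), 300 per arm, and 10–15% drop-out, which leaves 300 × 0.90 = 270 or 300 × 0.85 = 255 per arm. The article gives no SD, correlation or power for symptoms, so there is no figure of its own to reproduce on this point. Assumed: correlation ρ between baseline and a follow-up score of 0.3, 0.5 or 0.7, and SD ratio s = baseline SD / follow-up SD of 1, 0.85 or 0.7.

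**Which contrast.** With complete data, a difference score and a repeated-measures model that holds baseline as one level with a free group-by-time term give the same group contrast at each time point. One formula covers both.

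**Variances**, with follow-up SD = 1:

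- change: 1 + s² − 2ρs
- baseline-adjusted follow-up score: 1 − ρ²
- excess of the first over the second: (s − ρ)², which is never negative

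So the direction does not depend on the assumptions, apart from one degree of freedom, which is negligible at this size. With s = 1 the ratio of adjusted to change variance is (1 − ρ²)/(2(1 − ρ)) = (1 + ρ)/2.

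**Power with adjustment**, for an effect that the change analysis detects with 80% power: Φ(2.802/√ratio − 1.960), where 2.802 = 1.960 + 0.842.

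- Example, ρ = 0.5, s = 1: ratio 0.75; 2.802/0.866 − 1.960 = 1.275; power 0.899.
- Example, ρ = 0.5, s = 0.7: ratio 0.75/0.79 = 0.949; 2.802/0.974 − 1.960 = 0.916; power 0.820.

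| ρ | s = 1: ratio, power | s = 0.85: ratio, power | s = 0.7: ratio, power |
|---|---|---|---|
| 0.3 | 0.65, 93.5% | 0.75, 90% | 0.85, 86% |
| 0.5 | 0.75, 90% | 0.86, 86% | 0.95, 82% |
| 0.7 | 0.85, 86% | 0.96, 82% | 1.00, 80% |

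Read the other way, with s = 1: where the adjusted analysis has 80% power, the change analysis has about 62%, 68% and 73% at ρ = 0.3, 0.5 and 0.7.

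**Detectable difference** at 80% power, s = 1, ρ = 0.5, 270 per arm: 2.802 × √(2/270) = 0.241 SD for change, and 0.241 × √0.75 = 0.209 SD with adjustment. At 255 per arm the figures are 0.248 and 0.215 SD.

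**Imbalance.** Over repeated randomisation both analyses are unbiased. A simulation at 255 per arm gave bias within 0.002 SD and type I error of 0.045–0.058 for change and 0.050–0.054 with adjustment. Given an observed baseline difference D, with s = 1, the change estimate shifts by (1 − ρ)D. For D = 1.96 × √(2/255) = 0.174 SD the shift is 0.122, 0.087 or 0.052 SD at ρ = 0.3, 0.5 or 0.7. The type I error conditional on that imbalance is about 16%, 13% or 10% instead of 5%.

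**The case against.** The strongest objection is that this is one summary clause in a condensed article, and the covariates of a secondary model may be set out in a fuller document. Part of that stands. A reader might infer that baseline adjustment has been rejected, but the text neither names nor excludes it, and a model with baseline as covariate is compatible with the wording. What remains is not a missing detail. Two sections name change as the quantity of interest, one names the model class, and both natural readings give the less efficient contrast.

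A reader might also infer that the change analysis biases the health comparison. The documents do not support that. The trial is randomised, so the comparison is unbiased with correct type I error, and it shifts only conditional on an observed imbalance. Randomisation is blocked for physicians, with no balancing on symptom score stated, so a chance imbalance can occur.

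A third tempting inference is that the power gain is large whatever the correlation. It is not. Eligibility limits the baseline from below, since symptoms must justify full-time sick leave, and from above, through exclusions such as "severe pain (> 7 on a scale from 0 to 10" and its counterpart for sleep. Follow-up scores have no such limits, so a baseline SD below the follow-up SD is plausible, and at ρ = s the gain vanishes.

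Finally, the article shows that a threshold is applied at the visit, not that the numeric score is stored. That bears on the fix, not on the point.

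**Conclusion.** The point holds as one of efficiency and robustness. As worded, the symptom and disability analysis is never more precise than a baseline-adjusted one, and it is sensitive to chance imbalance. Across the assumptions shown, power rises from 80% to between about 80% and 93.5%. The upper end needs equal SDs and a low correlation, and the lower end arises when the correlation equals the SD ratio. The 80% starting point is a reference value, since the plan sets no power target for these outcomes.

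Only secondary outcomes are touched. Time to return to regular work, the sick leave day counts and the planned 600 employees are unaffected. The change is still worth making because the plan uses these scores to detect harm and to steer the economic analysis.

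**What to change.** State that symptom and disability scores at 1, 3, 8, 12 and 52 weeks are analysed in a repeated-measures model with group, time, group-by-time, the baseline score and baseline-by-time, or in an equivalent longitudinal model that constrains the baseline means to be equal. Report the adjusted group difference at each time point, and keep mean change as a descriptive summary.

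State also which baseline is used. The first questionnaire goes out after recruitment, when the employee may already know the allocation. The Interventions section has the physician consider Table 2 symptoms before randomisation, and the pain and sleep criteria imply a 0–10 rating at that visit. Use values recorded before the envelope is opened wherever they exist. For the functioning questionnaires, say when the baseline is completed relative to allocation.

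The cost is a sentence or two of analysis wording. No extra participants are needed, and no new data for any score already recorded at the visit. If the visit scores are not now kept, recording them is a small addition. The model estimate will no longer equal a simple difference in mean change, which the report should explain.

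### The repeated-measures general linear model named for symptoms and disability, in its classical form, leaves out employees with any missed questionnaire, which fits poorly with the intention-to-treat claim

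*Protocol article*

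**What the plan says.** All of this is in the protocol article.

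- **Statistical methods** names the method for the scores: "the change in symptoms and disability indices will be studied at various time points using general linear models for repeated measurements". The same section closes with "All analyses will be made based on an intention-to-treat principle".
- **Outcomes** lists symptoms and self-assessed functioning as other outcomes, after the two main ones. The questionnaire goes out right after recruitment and again at weeks 1, 3, 8, 12 and 52, which makes a baseline and five follow-ups. Sickness absence dates come separately, from occupational health unit records.
- **Sample size** allows for 10–15% drop-out in reaching 600 employees, 300 per group. The sizing criterion is return to regular work, not the questionnaire scores.
- **Discussion** says that a return to regular work at the wrong time, in either group, should become visible in secondary outcomes, including pain and functional status.
- **Blinding** states that allocation is open to the employee, the physicians and the interviewers.

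The article does not say how an employee with some missing questionnaires enters the repeated-measures analysis.

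**The concern.** The classical general linear model for repeated measurements works on one row per person, with one column per occasion. A person with an empty cell is removed from the whole analysis, including the occasions at which they did answer. With six occasions over a year and drop-out expected, that removes randomised employees from an analysis that the same section describes as intention-to-treat.

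Two things are at stake. One is precision on the symptom and disability outcomes. The other, more important, is selection. A complete-row analysis gives an unbiased comparison only if those with full data resemble those without, in both arms. Employees who recover poorly may stop answering, and because allocation is open they may do so at different rates in the two groups. These scores are the Discussion's safeguard against a badly timed return to work, so losing the poor recoverers would weaken it. The Economic evaluation section also makes its type of analysis depend on whether the health outcomes differ between the groups, so the effect would carry over there.

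**Working it through.** **Inputs from the article.** 600 employees, 300 per group; drop-out 10–15%; five follow-up questionnaires after baseline; "The power of the study is aimed at 80%, and the level of significance at 0.05".

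**Assumed inputs, not in the article.** The drop-out rate applies to the questionnaires; the test is two-sided; the treatment effect is 0.2 SD at every follow-up; the within-person correlation ρ is 0.5 or 0.7; per-wave missingness is as stated below.

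**Step 1: the plan's own figure.** The 600 cannot be reproduced from the article alone, because no base rate is given for the 10-point difference. It is attainable. With 17% against 27%, no continuity correction and pooled variance:

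n per arm = [1.960·√(2·0.22·0.78) + 0.842·√(0.17·0.83 + 0.27·0.73)]² / 0.10² = 268.2, so 269. Then 2·269/0.90 = 597.8, so 598.

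This concerns return to work only. It says nothing about power for the scores.

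**Step 2: employees lost at the stated drop-out.** If each drop-out misses at least one wave and nobody else does:

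- 600 × 0.10 = 60 lost, 540 kept (270 per arm)
- 600 × 0.15 = 90 lost, 510 kept (255 per arm)

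**Step 3: employees lost if waves are also skipped.** With drop-out d and independent per-wave missingness m, the complete proportion is (1 − d)(1 − m)⁵.

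- d = 0.10, m = 0.05: 0.90 × 0.774 = 0.696, so about 30% lost
- d = 0.15, m = 0.05: 0.85 × 0.774 = 0.658, so about 34% lost
- d = 0, m = 0.10: 0.90⁵ = 0.590, so 354 kept and 246 lost

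The values of m are illustrations; the article gives none.

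**Step 4: power for the group effect over five follow-ups.** The mean of five scores has variance (1 + 4ρ)/5 in SD² units, so for complete rows power ≈ Φ(0.2/√(2(1 + 4ρ)/(5n)) − 1.96). With ρ = 0.5 and n = 270, this is Φ(0.2/0.0667 − 1.96) = Φ(1.04) = 0.85. Simulation (4,000 runs per cell, 300 randomised per arm) gave:

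| Missing data | ρ | Complete rows only | All available scores | Loss (points) |
|---|---|---|---|---|
| 10% drop-out | 0.5 | 0.850 | 0.876 | 2.6 |
| 10% drop-out | 0.7 | 0.756 | 0.789 | 3.3 |
| 15% drop-out | 0.5 | 0.826 | 0.866 | 4.0 |
| 15% drop-out | 0.7 | 0.726 | 0.782 | 5.6 |
| 10% missing per wave | 0.5 | 0.672 | 0.884 | 21 |
| 10% missing per wave | 0.7 | 0.581 | 0.801 | 22 |

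These figures measure lost precision only. The size of any selection bias was not computed; it would need assumptions about who stops answering, and the article gives no basis for them.

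**The case against.** The best reply is that the article nowhere says incomplete cases are removed. Listwise deletion belongs to the classical implementation. The phrase used can be read loosely enough to cover a mixed model on all available scores, the only stated rule on analysis sets is intention-to-treat, and handling of missing scores is commonly left to a fuller plan. This stands against any claim that the protocol commits itself to dropping randomised employees. It does not remove the point, because a method is named and its usual meaning conflicts with the stated principle.

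A second reply is that the sample size already allows for 10–15% drop-out. That protects the number of evaluable employees for the return-to-work criterion. It does not protect against selection, and the scores were not what the study was sized on.

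A reader might go further and infer that a linear model is also wrongly fixed for total sick-leave days, with employees who leave the company counted as having low absence. The article does not support that. The sentence mentioning the day totals attaches the model to something else: "the associations between the outcomes and background variables will be analysed using general linear models". Unequal time at risk is not described either, since follow-up is a set one and two years from records. A linear comparison of mean days also holds its error rate: in simulations with assumed skewed counts and 300 per arm, it rejected a true null 4.8–5.5% of the time. With full follow-up it lost only about 0.5–1.5 points of power against a negative binomial model.

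**Conclusion.** The point holds for the symptom and disability scores only. As classically implemented, the named model would leave out 60–90 of 600 randomised employees at the article's own drop-out rate, taking that rate to apply to the questionnaires. The cost would be about 3–6 points of power under the assumed effect and correlations. That loss is modest. The stronger reason to act is the risk of selection in outcomes that the Discussion uses as a check on the intervention; its size is unknown.

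The larger losses, 30–34% of employees or 246 of 600, should not be read as predictions. They show how quickly complete rows disappear when single waves are skipped, and they rest on per-wave rates that the article does not give. The main outcomes are not affected: time to return to work has its own survival analysis, and absence days come from records.

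**What to change.** In Statistical methods, replace the repeated-measures wording with a linear mixed model for repeated measures. It should use every available follow-up questionnaire from all randomised employees, in the group to which they were allocated. Include treatment, visit, treatment-by-visit and the baseline score as covariate, and report the group difference at each visit. State how a missing baseline score is handled, since the baseline questionnaire is sent after recruitment and an employee without one would otherwise drop out of a baseline-adjusted model.

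The cost is a change of wording; no new data are needed and standard software suffices. The model rests on a missing-at-random assumption, which should be stated. It is weaker than what a complete-row analysis generally needs, but it does not cover employees who stop answering for reasons unrelated to anything recorded. No change to the analysis of sick-leave days is asked for here.
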